## Abstract

**Introduction:**

Changes in social and lifestyle factors have led to increasing rates of metabolic and mental health problems. We hypothesise that a transformation of the current maternal and child health system is required to deliver interventions that effectively promote a good start to life in populations at risk of metabolic and mental health problems. We describe a single-arm implementation study ‘Healthy Early Life Moments in Singapore’, which aims to examine whether an integrated lifestyle intervention initiated at preconception and continuing throughout pregnancy and postpartum periods can improve the metabolic and mental health of overweight and obese women, and improve early child growth.

**Methods and analysis:**

This single-centre implementation trial is conducted at KK Women’s and Children’s Hospital, Singapore. The trial aims to recruit 500 women, aged 21–40 years with a body mass index of 25–40 kg/m^2^ who plan to get pregnant, with interventions delivered before conception, until 18 months postdelivery. Primary outcomes comprise pregnancy rate, maternal metabolic and mental health status. Secondary outcomes include maternal reproductive health, pregnancy outcomes and offspring growth. The intervention will be delivered using a mobile health application, to provide anticipatory guidance, raise awareness and guide goal-setting on lifestyle behaviours that include diet, physical activity, mental wellness and sleep hygiene from preconception to postpartum. Women who conceive within 1 year of recruitment will be followed through pregnancy and studied with their infants at six-time points during the first 18 months of life. Questionnaires, anthropometric measurements and multiple biosamples will be collected at each visit.

**Ethics and dissemination:**

The study has been approved by the Centralised Institutional Review Board of SingHealth (2021/2247). Written informed consent will be obtained from all participants. The findings will be published in peer-reviewed journals and disseminated to national and international policy makers.

**Trial registration number:**

NCT05207059.

STRENGTHS AND LIMITATIONS OF THIS STUDYHealthy Early Life Moments in Singapore (HELMS) aims to examine the impact of integrated interventions, initiated preconceptionally and continued throughout the pregnancy and postpartum phases, on metabolic and mental health of women who are overweight or obese.Extensive biosampling and detailed phenotyping of mother, father and child will allow longitudinal assessment of changes in health behaviours including diet, physical activity and sleep, maternal metabolic profile and depression risk.This will provide an important platform for biomarker discovery, validate integrated HELMS interventions and pave the way for new guidelines for lifestyle programmes from preconception to postpartum stages.The main limitation of this study design includes the inability to distinguish between the effect of an intervention, a placebo effect and the effect of natural history.HELMS is a single-centre study of the Asian population, involving only English-speaking participants, so external validity may be limited to this population, and caution should be exercised in generalising results across different settings and populations.

## Introduction

Non-communicable diseases (NCDs) represent the predominant cause of morbidity and mortality worldwide.^1^ Rapid urbanisation, unhealthy diet and sedentary lifestyles have led to an epidemic of metabolic diseases, which are the main drivers of NCDs.^1^ Coupled with this metabolic epidemic is a rising rate of mental disorders, especially depression, as the leading cause of disability worldwide that commonly affects women.^2^ Both metabolic and mental disorders are interrelated, with their co-occurrence frequently observed in individuals living with obesity.^3 4^ The short-term and long-term health risks of maternal obesity and depression in mothers and their children are well documented.^5–7^ Women living with obesity and mental health conditions are at increased risk of infertility, adverse obstetric outcomes and postpartum cardiometabolic complications; and their children are also susceptible to obesity, metabolic disease and psychosocial disturbances in childhood and adolescence.^5–7^ In Singapore, almost one-third of women are overweight or obese (body mass index (BMI) 25–29 kg/m^2^ :17%; BMI ≥30 kg/m^2^ :13%) before pregnancy,^8^ while one in ten women experience depression before, during and after pregnancy.^9 10^

To mitigate the impact of maternal obesity and depression, various intervention strategies targeting antenatal and postpartum periods have been studied. These include setting Specific, Measurable, Achievable, Relevant, Time-Bound goals, providing healthy lifestyle counselling or group-based education, perinatal mental health interventions and providing health service support.^11–13^ However, these antenatal and immediate postpartum-phase focused interventions have had modest success,^14 15^ only some showing improvements in eating behaviour, physical activity or weight status,^11 16–18^ and most failing to prevent adverse mother–offspring outcomes such as gestational diabetes mellitus and macrosomia. This could be attributed to the relatively short duration of the intervention, the lack of continued care from preconception and intervention only beginning in the antenatal and postpartum periods, which may be too late to produce any meaningful impact.

There is increasing focus on interventions during the preconception period, especially for women living with obesity, who are susceptible to both metabolic and mental disorders.^3 19^ Such interventions not only improve the health of the mother, but also provide potential health benefits to the next generation through an improved environment for embryo and fetal development.^20 21^ The preconception period represents a unique opportunity where women are motivated to make a positive change to attain optimal pregnancy outcomes.^22^ So far, preconception lifestyle interventions have demonstrated positive maternal behaviour changes, such as increased intake of multivitamins, vegetables and other dietary changes, increased physical activity, as well as smoking cessation and reduced alcohol consumption, resulting in a reduction in BMI and gestational weight gain, higher clinical pregnancy rate and lower preterm delivery.^23–25^ This has led to improved knowledge, self-efficacy and control.^26^ Furthermore, women who achieved at least 5% wt loss during such interventions had better cardiometabolic health based on glycaemic and lipid measures 6 years later.^25^

Taken together, this suggests that adopting a life-course perspective in the healthcare model with a continuum of care provided before, during and after pregnancy has the potential to address the trajectory of increased metabolic and mental disorder risk throughout these life stages. Acting upstream before conception to optimise health is crucial to improving reproductive potential while reducing the social and health implications resulting from unplanned pregnancies. Modifying current antenatal care services by empowering women in preparation for pregnancy and childbirth is critical for the well-being of both mother and baby. Optimising postpartum recovery and readiness, and nurturing infants through optimal feeding practices and growth monitoring are important for promoting virtuous life cycles of health in an individual and breaking vicious life cycles of NCDs for the next generation.^27^

### Goals and aims

We envision an integrated life-course approach with a continuum of care that encompasses preconception preparation, pregnancy optimisation, along with postpartum synchronisation of maternal–child health services in the first 18 months of life. Connecting the preconception, pregnancy and postpartum journeys will achieve synergism in producing greater behavioural change and beneficial outcomes not only for women, but also for the child and family.^19^ Therefore, the goal of Healthy Early Life Moments in Singapore (HELMS) is to develop and implement a life-course model of care (MOC) starting from preconception to pregnancy and postpartum phases, to achieve optimal metabolic and mental health for both mother and child. This MOC focuses on preventive healthcare, a time where the cost-effectiveness of the intervention is likely to be maximum,^28^ and represents the clinical translation of early developmental programming based on the Developmental Origins of Health and Disease paradigm.^20^

In this study, the overarching aim is to examine whether an integrated intervention beginning preconceptionally and continuing throughout the pregnancy and postpartum phases can improve the metabolic and mental health of women living with obesity, as well as optimise offspring growth and development. At each life-course phase, the study addresses specific hypotheses. We hypothesise that the HELMS MOC lifestyle interventions will promote the metabolic and mental health of overweight and obese women, and thus optimise (1) reproductive outcomes during preconception, (2) obstetric outcomes during pregnancy and (3) postpartum physical and mental well-being, and healthy feeding habits and growth during infancy. We also hypothesise that greater improvements in metabolic and mental health will be observed in obese women with obesity than in those who are overweight. An overview of the study framework is shown in figure 1.

**Figure 1 F1:**
[figure not shown]
The Healthy Early Life Moments in Singapore (HELMS) framework, comprising preconception, pregnancy and postpartum dyad care. Through maternal behavioural intervention, the overarching aim is to improve metabolic and mental health in women living with obesity, and to improve early child growth. Specifically, HELMS aims to improve women’s fertility, obstetric outcomes, physical and mental recovery from birth, feeding habits and growth of the child.

## Methods and analysis

### Trial design and setting

This study represents a model of implementation to demonstrate the value of adopting a life-course approach and integrated care to maternal–child health. It is conceptualised as a single-arm trial, with a targeted intervention implemented in a group of women living with obesity who are trying to conceive within 1 year after recruitment. The longitudinal intervention will be performed from preconception, throughout pregnancy until 18 months postpartum in the KK Women’s and Children’s Hospital (KKH), Singapore. The protocol is written following the SPIRIT (Standard Protocol Items: Recommendations for Interventional Trials) guidelines. Written informed consent will be obtained from all participants at the recruitment.

The flow of the trial is shown in figure 2. Participants will be reviewed at multiple time points from preconception through pregnancy, and both participants and their infants will be followed for the first 18 months after delivery, with extensive biosampling and detailed phenotyping performed longitudinally. Following informed consent at the first preconception clinic visit, participants will complete a set of questionnaires that assess baseline demographics, diet practices, physical activity, sleep, emotion and sexual health. Anthropometric measurements will be taken, together with biosample collection, including blood for a standard 75 g oral glucose tolerance test and stool. Participants will receive a doctor’s consultation, along with prescription of a standard preconception supplement, digitised preconception care and healthy lifestyle guidance. The second preconception clinic visit will take place 6 months later, with questionnaires and measurements being performed, and compliance with the intervention being reviewed. Phone contact will be made 3 and 9 months after recruitment to help participants maintain focus on their preconception health and lifestyle goals, and to remind them to perform a urine pregnancy test if periods are missed. If they do not become pregnant, an exit visit will be conducted at 12 months with questionnaires, measurements and biosampling, followed by appropriate evaluations and subfertility referrals thereafter. Participants who become pregnant will be seen between 6 and 10 weeks of gestation at the first pregnancy visit. Questionnaires, measurements and biosampling will again be performed. The second HELMS pregnancy visit will be at 24–28 weeks, and the final HELMS visit in pregnancy will be at 32–36 weeks. Continuous antenatal care and healthy lifestyle guidance during pregnancy will be provided throughout the trimesters. At delivery, maternal and infant biosampling, including placenta collection, will be performed. In the postpartum dyad phase, there will be six visits over an 18-month period, according to the infant vaccination schedule, at 1–2 weeks, 6–8 weeks, 4, 6, 12 and 18 months. An ongoing intervention tailored to this postpartum dyad phase will be delivered, together with questionnaires, measurements and biosampling for the mother and child at each visit. Throughout the study, participants will be asked to log their weight and supplement intake weekly in a digital calendar. For the partner, lifestyle and anthropometric measurements will be collected during the preconception, pregnancy and postpartum periods; blood will be collected once during the pregnancy phase. Meanwhile, partners will be passively engaged in the intervention by receiving the same set of digitised intervention materials. A feedback survey on the HELMS programme will be performed at the end of each preconception, pregnancy and postpartum phase.

**Figure 2 F2:**
[figure not shown]
HELMS study flow diagram. Preconception visits are coloured green, pregnancy visits pink and postpartum visits blue. HELMS, Healthy Early Life Moments in Singapore.

### Patients and public involvement

We have conducted in-depth face-to-face interviews with preconception, pregnant and postpartum women who were overweight and obese to understand their needs throughout the preconception-pregnancy-postpartum journey, enablers and barriers to a healthy lifestyle, intervention preferences and delivery methods. This work enabled the development of the intervention package and dissemination plans.^29^

### Participants and recruitment

Potential participants from the public or KKH (patients/staff) or referred from other healthcare institutes who fulfil the inclusion criteria will be invited to participate in the HELMS study. KKH houses the largest Obstetrics and Gynaecology department in Singapore, managing approximately 12 000 deliveries a year with patients made up of a wide sociodemographic spectrum. Invitation letters, emails, messages, webpages, brochures and posters will be used for advertising. Interested women can contact the study team by email or phone.

Inclusion criteria include (1) a woman who plans to conceive in the next 12 months; (2) BMI 25–40 kg/m^2^; (3) age 21–40 years; (4) Chinese, Malay, Indian ethnicity or any combination of these three ethnic groups; (5) intending to reside in Singapore for the next 4 years; (5) can access the Internet through any digital platform and (6) can provide written informed consent. Exclusion criteria include (1) currently pregnant; (2) difficulty in understanding the English language; (3) known type 1 or type 2 diabetes; (4) being on anticonvulsant medication, oral steroid, contraception or fertility medication in the past 1 month; (5) on HIV or Hepatitis B or C medication in the past 1 month. If a woman is pregnant within 1 month from the baseline visit, they will be censored from the analyses. If a woman has a pregnancy loss and wishes to rejoin the study, she will be recharacterised at the preconception baseline visit at least 1 month after a negative urine pregnancy test and will receive intervention as before.

Women who suffer from a miscarriage or termination event, experience multiple pregnancies, with fetal congenital anomalies, cannot comply with the study protocol or wish to discontinue their participation will be withdrawn from the study.

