### Planned analyses

Continuous variables will be presented as means and SD, or medians and 25th–75th centiles, as appropriate. Categorical variables will be presented as numbers and percentages. The pregnancy rate will be determined by the number of women who became pregnant (defined as stated previously) divided by the total number of women who completed the 1-year follow-up during the preconception phase. The time to pregnancy (TTP) will be estimated by the number of menstrual cycles required to achieve pregnancy over 1 year of follow-up. We will use the discrete-time proportional hazards model, which analyses TTP as a discrete scale based on the number of menstrual cycles, to estimate the fecundability ratio (FR) and the 95% CI,^43 44^ accounting for left truncation and right censoring. For the other two coprimary outcomes, a linear mixed effects model will be used to examine changes in means between the baseline and follow-up metabolic markers and EPDS scores, with adjustment for baseline potential confounders (including partner’s characteristics) and duration of the intervention received. In addition to the pre–post comparison of outcomes stated above, differences in pregnancy and birth outcomes will also be compared with a similar observational cohort in Singapore called Singapore PREconception Study of long-Term maternal and child Outcomes (S-PRESTO),^45^ using multiple linear or logistic regression models, adjusting for potential confounders. These confounders, such as age, ethnicity and education, will be determined from literature review, directed acyclic graph and/or observed statistically significant associations with exposures and outcomes.

We will impute missing data using multiple imputation analyses by chained equations.^46^ The number of imputations will be determined based on a percentage of missing values,^47^ and the results of total imputations will be pooled using Rubin’s rule.^48^ To determine whether the imputation of the missing data may have affected the results, we will perform sensitivity analyses on participants with a complete set of data.

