### Sample size calculation

Based on the S-PRESTO study,^45^ which is an observational cohort recruited from preconception and followed up through postpartum periods, preconception overweight or obese women (BMI ≥25 kg/m^2^) had a 38% pregnancy rate, while those with normal weight (BMI 18.5–24.9) had 47% pregnancy rate. Among overweight and obese women, those with healthy metabolic profiles characterised by absence of the metabolic syndrome or insulin resistance had a 52% pregnancy rate. We anticipated that HELMS intervention will improve overweight or obese women’s pregnancy rate from 38% to 50% within 12 months of trying. Using a two-sided α level of 5% and a power of at least 90%, 400 participants are needed in the preconception phase, leading to 200 pregnancies. Considering a 20% drop-out rate, 500 participants are required for recruitment. We estimated that 15% of women will experience pregnancy loss and another 10% drop-out, leaving 150 dyad pairs to be followed.

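### Withdrawing women who cannot comply, with a completers-only denominator, selects the primary pregnancy rate on adherence; the new baseline after a pregnancy loss is not reconciled with withdrawal

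*Protocol article*

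**What the plan says.** Two adjoining paragraphs of the protocol article, under Participants and recruitment, govern who leaves and who returns.

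- **Re-entry.** "If a woman has a pregnancy loss and wishes to rejoin the study, she will be recharacterised at the preconception baseline visit". Her return must follow a negative test by a month or more, and the programme is then given again.
- **Withdrawal.** The next paragraph begins "Women who suffer from a miscarriage or termination event, experience multiple pregnancies, with fetal congenital anomalies, cannot comply with the study protocol" and ends by saying that those who "cannot comply with the study protocol or wish to discontinue their participation will be withdrawn from the study".

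Neither paragraph refers to the other.

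Planned analyses defines the primary rate. The numerator is given first: "The pregnancy rate will be determined by the number of women who became pregnant". The denominator is limited to completers, since that count is to be "divided by the total number of women who completed the 1-year follow-up during the preconception phase". Outcomes and assessments sets the window at one year from the baseline assessment. The metabolic and EPDS coprimary outcomes are analysed as changes from baseline in linear mixed models.

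Sample size calculation takes 38% as the reference rate and 50% as the target. It plans 500 recruits, 20% drop-out, 400 women in the preconception phase and 200 pregnancies. It then states: "We estimated that 15% of women will experience pregnancy loss and another 10% drop-out", which leaves 150 mother-child pairs.

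**The concern.** There are two issues, and the first matters more.

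**Selection on adherence.** Not complying is a stated reason for withdrawal, and the primary rate is computed only among women who finish the preconception year. Taken together, a woman who stops complying before that point drops out of the primary result. The trial describes itself as a model of implementation, so failure to keep up with the programme is part of what it should measure. The design has one arm and its target rests on an external 38%. A shift caused by who remains in the denominator therefore has no concurrent group in which to cancel.

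**Unsettled baseline.** A woman who rejoins after a loss is characterised again after months of intervention. If that second visit serves as her baseline, her change in metabolic markers and EPDS is measured from an already treated state. The article does not say which baseline or which one-year window then applies.

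**Working it through.** **1. The plan's own counts reproduce.** 400 / (1 - 0.20) = 500 recruits; 400 × 0.50 = 200 pregnancies; 200 × (1 - 0.15 - 0.10) = 150 pairs. The 200 pregnancies in 400 women show that the sponsor treats women who conceive early as having completed the preconception phase. That reading is used below.

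**2. Completers-only denominator.** Inputs from Sample size calculation: N = 500, w = 100 drop-outs, true rate 38%, hence 500 × 0.38 = 190 pregnancies. The drop-outs' own conception rate r is not in the article and is an assumption. The 100 are drop-outs of all kinds, not only women who could not comply.

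Observed rate = (190 - w × r) / (500 - w). With w = 100:

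| Assumed r | Calculation | Completers' rate | Shift |
|---|---|---|---|
| 38% | 152 / 400 | 38.0% | 0 |
| 20% | 170 / 400 | 42.5% | +4.5 points |
| 10% | 180 / 400 | 45.0% | +7.0 points |
| 0% | 190 / 400 | 47.5% | +9.5 points |

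With fewer women lost the shift shrinks. At w = 50 the last three rows become 180/450 = 40.0%, 185/450 = 41.1% and 190/450 = 42.2%.

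For scale, suppose the rate were tested against a fixed 38% with n = 400 (an assumption, as the article does not name the test). The upper 2.5% binomial cut-off is 172 pregnancies. The chance of reaching it is 2.3% at 38%, 44% at 42.5%, 80% at 45% and 97% at 47.5%.

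**3. The same data with everyone kept.** Take the planned 200 pregnancies in 400 completers, which is 50.0%. Over all 500 women the rate is 200/500 = 40.0% if no drop-out conceived, (200 + 38)/500 = 47.6% if they conceived at 38%, and (200 + 50)/500 = 50.0% if at 50%.

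**4. Re-entry and the pregnancy rate.** At the plan's 15% loss there are 0.15 × 152 = 22.8 losses at a 38% rate and 0.15 × 200 = 30 at 50%. Assume that all rejoin, that 60% conceive again, and that each return counts as an extra attempt:

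- (152 + 22.8 × 0.6) / (400 + 22.8) = 165.68 / 422.8 = 39.2%
- (200 + 30 × 0.6) / (400 + 30) = 218 / 430 = 50.7%

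Both move by about one point. If each woman is counted once, neither moves.

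**5. Withdrawn losses.** If women with a loss were instead removed from numerator and denominator, the rates would fall: (200 - 30)/(400 - 30) = 45.9% and (152 - 22.8)/(400 - 22.8) = 34.3%.

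**6. Re-entry and the coprimaries.** No arithmetic is possible because the article gives no expected change. Only the direction can be argued: if the intervention works, a baseline taken after earlier exposure would probably make the measured change smaller.

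**The case against.** The defence has good points, and a reader could be tempted further than the article allows.

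- **A contradiction?** A reader might infer that the two paragraphs contradict each other. A wish to rejoin presupposes having left, so withdrawal followed by optional re-entry is a natural reading. This stands: the paragraphs are unreconciled, not shown to conflict.
- **Double counting?** A reader might infer that women who have already conceived once can enter the numerator twice. The definition counts women, and a woman who conceived and then lost the pregnancy is already one of them. The sample size also subtracts losses without adding re-entries back. Dividing conceptions by women would give larger figures, but the article defines no such ratio.
- **Poorer responders removed?** The article says only that these women cannot comply. That they would conceive less often is an assumption, which is why the table starts at no difference.
- **Always favourable?** No. Most named withdrawal reasons apply to women who have conceived, and dropping losses would lower the rate. A treated second baseline would probably understate the coprimary change.
- **A contrast with S-PRESTO's rules?** The article does not describe how that cohort handled losses or non-compliance, so nothing can be built on it.
- **Existing safeguards.** The time-to-pregnancy model allows right censoring, so withdrawn women can contribute cycles there. The mixed models adjust for duration of intervention, which bears on earlier exposure. Multiple imputation is planned. These help in their own analyses, but none changes a crude primary rate defined on completers.
- **Detail for a fuller document.** How a returning woman is analysed could be settled in the full protocol or analysis plan. That is fair for the convention itself. The withdrawal rule, the re-characterisation at baseline and the completers' denominator are all stated here and can be judged here.

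**Conclusion.** The concern holds for the denominator and, more narrowly, for re-entry.

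- **Denominator.** Applied as written, the withdrawal rule and the completers' denominator select the primary rate on adherence. At the planned 20% drop-out the upward shift runs from 0 to 9.5 points, against a planned improvement of 12 points (38% to 50%). Where it falls depends on the drop-outs' conception rate, which the article does not give, and on how many of the 100 leave before the year ends. The upper end requires that none of them conceives.
- **Re-entry.** The two paragraphs need reconciling, and the choice of baseline affects the coprimary changes by an amount that cannot be computed from the article. For the pregnancy rate the effect is about one point under generous assumptions, and zero on the plain wording.

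The article does not support a claim that fertile women are counted twice, that poor responders are removed, or that all these rules favour the intervention. This should be corrected, but it does not invalidate the design.

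**What to change.** 1. Reconcile the withdrawal and re-entry statements in Participants and recruitment, so that it is clear whether and how a woman with a loss may return. Which participation rule stands is for the sponsor to decide.
2. For the analysis, let each woman enter once, from her first enrolment and first baseline. Count her first confirmed pregnancy even if it is later lost. The separate rule on pregnancies within one month of baseline is not affected. Report second attempts separately.
3. Distinguish stopping the intervention from leaving the analysis. Keep women who stop complying or are withdrawn in the primary denominator, with all data collected.
4. Seek 12-month pregnancy status by a brief phone contact where consent allows; calls at 3 and 9 months are already planned. Censor or impute the remainder, and report the completers' rate as a sensitivity analysis.

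**Cost.** A protocol clarification, revised analysis wording and slightly more phone follow-up. Second-attempt data leave the primary analysis, and the primary rate may look less favourable.
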